## Abstract

**Background:**

Most frail older persons are living at home, and we face difficulties in achieving seamless monitoring to detect adverse health changes. Even more important, this lack of follow-up could have a negative impact on the living choices made by older individuals and their care partners. People could give up their homes for the more reassuring environment of a medicalized living facility. We have developed a low-cost unobtrusive sensor-based solution to trigger automatic alerts in case of an acute event or subtle changes over time. It could facilitate older adults’ follow-up in their own homes, and thus support independent living.

**Objective:**

The primary objective of this prospective open-label study is to evaluate the relevance of the automatic alerts generated by our artificial intelligence–driven monitoring solution as judged by the recipients: older adults, caregivers, and professional support workers. The secondary objective is to evaluate its ability to detect subtle functional and cognitive decline and major medical events.

**Methods:**

The primary outcome will be evaluated for each successive 2-month follow-up period to estimate the progression of our learning algorithm performance over time. In total, 25 frail or disabled participants, aged 75 years and above and living alone in their own homes, will be enrolled for a 6-month follow-up period.

**Results:**

The first phase with 5 participants for a 4-month feasibility period has been completed and the expected completion date for the second phase of the study (20 participants for 6 months) is July 2020.

**Conclusions:**

The originality of our real-life project lies in the choice of the primary outcome and in our user-centered evaluation. We will evaluate the relevance of the alerts and the algorithm performance over time according to the end users. The first-line recipients of the information are the older adults and their care partners rather than health care professionals. Despite the fast pace of electronic health devices development, few studies have addressed the specific everyday needs of older adults and their families.

**Trial Registration:**

ClinicalTrials.gov NCT03484156; https://clinicaltrials.gov/ct2/show/NCT03484156

**International Registered Report Identifier (IRRID):**

PRR1-10.2196/14245

## Introduction

### Background

We are facing an increase in the number of older adults with a high prevalence of functional and cognitive decline [1,2]. Early preventive strategies could stabilize or even prevent this decline [1,3,4]. Most frail older individuals are living at home, and we recognize the difficulties in achieving seamless in-home monitoring for the early detection of subtle health changes over time [1,2]. Clinical assessments are usually performed too far apart and outside the person’s own environment. These evaluations rely on self-reported information affected by recall bias and poor reliability [5]. A follow-up before functional or cognitive impairment could have a positive impact through personalized care plans when symptoms can still be treated.

Technology could potentially help to overcome this shortfall in terms of follow-up by providing continuous sensitive and ecologically valid measures. Several real-life studies confirm the relationship between sensor-based monitoring of physiological parameters and health outcomes [6,7]. The follow-up of health changes over time could also support the living choices made by older individuals and their care partners. Some people abandon their desire for independence in favor of the more reassuring environment of a dedicated living facility much earlier than necessary. Nevertheless, although information and communication technologies have been shown to be effective in many medical situations [8], few solutions are proposed to monitor the intrinsic capabilities of older adults in their own homes [9-11]. Beyond *organ-based* telemonitoring solutions (eg, heart failure or diabetes monitoring), a comprehensive function-based monitoring solution could be beneficial to avoid the overlap and multiplication of technical tools in this complex population.

We hypothesized that a network of low-cost sensors could trigger alerts if an acute and unusual event is detected in activities of daily living—ADL (eg, use of the bathroom at night, followed by several hours of immobility) or subtle changes over time (eg, disorganization in stereotypical habits). Our solution based on nonintrusive sensors could provide relevant information to care partners and health professionals to support the monitoring of older people in their homes, thus promoting independent living.

### Objectives

The primary objective is to evaluate the relevance of the alerts automatically generated by a sensor-based solution and the evolution of the algorithm’s performance over time as judged by the recipients: older adults, care partners, and professional support workers. The secondary objective is to evaluate the ability of this solution to detect functional and cognitive decline and major medical events.

## Methods

### Study Design

This is a prospective open-label study. We will enroll 25 participants for a 6-month follow-up period. To allow for modifications to the solution in the event of technical issues before wider use, the first 5 participants are enrolled for a preliminary 4-month phase before the 6-month regular follow-up period. The enrollment process is spread out over time for the same reason. The flow chart is presented in Figure 1.

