**Figure 2 figure2:**
[figure not shown]
Presentation of the overall solution. In this configuration, the solution comprises 4 passive infrared sensors to monitor activity (bedroom, kitchen, living room, and entrance hall); 1 contact sensor on the main entrance door; 1 cookie sensor on the fridge to monitor door opening; a pendant (or wristband) with a push-button emergency alarm; and a live intercom system (device in the left of the illustration) for direct audio communication with the support center (calling function).

The following data will be monitored: presence (yes/no) in specific rooms, for example, rooms associated with eating, bathing, and sleeping; time spent outdoors; total activity inside the home (estimated by the average number of sensor activations per day) [6]; fridge use; and sleeping patterns.

The solution can trigger 2 different types of alerts. The first consists of *conventional alerts*. They are generated by the participants using an alarm push button or through the intercom system. The second type of alert assessed in this project is automatically triggered by our artificial intelligence algorithm after an initial learning phase (eg, gradual change in sleeping pattern). The sensor-based alerts and the use of the Live intercom calling function are both directed to a telecare worker on a nationwide telecare platform (IMA/Serena) all 7 days a week and 24 hours a day. The telecare worker can suggest a range of actions, from direct contact with the older individual to a phone call to the care partner or to emergency services. The first month is dedicated to algorithm learning: all sensors are functional, but no automatic alert is generated from the platform. Activity data relating to sleeping, eating, and time spent outdoors, and so on, are recorded and analyzed. After the first month, there will be sufficient data to detect unusual behaviors and eventfully trigger an alert. The algorithm used to perform real-time detection of behavioral anomalies is described elsewhere [14].

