### Follow-Up Procedure

The first 5 participants are enrolled for a total of 10 months (an initial 4-month period followed by a 6-month follow-up period) and the other 20 participants for 6 months. An installation visit will take place in the days following enrollment. A remote follow-up evaluation will be carried out over the phone by a CRA every 2 months after the baseline assessment (see Table 2). The last visit will be conducted by the CRA in the participant’s home after 6 months. For the first 5 participants enrolled in the study, the baseline for data analysis is defined as the beginning of the 6-month follow-up period at the end of the first preliminary 4-month period which is dedicated to technical feasibility. The proper regulatory and ethical conduct of the study is monitored by a clinical research technician, acting on behalf of the University Hospital.

**Table 2 table2:** Data collection.

Variables	Preinclusion (CRA^a^, in-person)	Baseline T0 (investigator)	T2 months (CRA, phone)	T4 months (CRA, phone)	T6 months (CRA, in-home visit)
Informed consent	✓	✓	—^b^	—	—
Sociodemographic data	—	✓	—	—	—
ADL^c^, IADL^d^, MMSE^e^	—	✓	—	—	✓
Frailty criteria, SPPB^f^	—	✓	—	—	✓
Acceptability questionnaire, EQ5D^g^	—	✓	✓	✓	✓
Major medical events	—	✓	✓	✓	✓
Sensor data	—	Continuous measures	Continuous measures	Continuous measures	Continuous measures

^a^CRA: clinical research assistant.

^b^Data not collected.

^c^ADL: activities of daily living.

^d^IADL: instrumental activities of daily living.

^e^MMSE: mini mental state evaluation.

^f^SPPB: short physical performance battery.

^g^EQ5D-3L: EuroQol 5D score to describe and value health, quality of life questionnaire.

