### Sample Size

To the best of our knowledge, no comparable study has evaluated a similar primary endpoint in this population. Therefore, a formal sample size calculation could not be carried out. However, we can expect more than 1 alert per individual during the 6-month period. The predictive value calculations (estimation of legitimate alerts) will be based on numbers over 25, a 95% CI accuracy of at least ±20%. As an example, if a participant triggers 2 alerts on average during the study, with half of them rated as valid, a 95% CI close to 35.5% to 64.5% can be expected.

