### Statistical Analysis

The main analysis will be an intent-to-treat analysis. The quantitative outcomes will be estimated with 95% CI. Quantitative variables will be expressed by mean values and standard deviations. The 6-month follow-up period for the 25 participants will allow us to record the number and frequency of alerts generated by the solution. A total of 3 positive predictive value (PPV) calculations (estimation of legitimate alerts) will be done (95% CI, thanks to end users’ feedback for the overall follow-up period and for each 2-month follow-up period: 0-2 months, 2-4 months, and 4-6 months) to estimate the progression of algorithm performance. For the secondary objective, we will also analyze these 3 periods to evaluate the performance of the automatic alerts in detecting changes in functional or cognitive autonomy or major events (sensitivity, specificity, predictive value, and receiver operating characteristic [ROC] curves). Alerts will be addressed with both a binary approach (no alert vs 1 alert to estimate sensibility, specificity, PPV, and negative predictive value) and a continuous approach (number of alerts over the period to plot an ROC graph and estimate the area-under-the-curve). The Department of Epidemiology at our University Hospital will conduct statistical analyses using SAS version 9.4 (SAS Institute, Inc).

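### The overall PPV pools 5 feasibility-phase homes, which have 4 months of prior operation, with 20 newly equipped homes, so alone it may overstate performance in new homes

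*Protocol article*

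**What the plan says.** All references are to the protocol article.

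- **Study Design** sets the total: "We will enroll 25 participants for a 6-month follow-up period". It also explains the early start of some homes: "To allow for modifications to the solution in the event of technical issues before wider use, the first 5 participants are enrolled" for a preliminary 4 months ahead of regular follow-up. Enrolment as a whole is staggered for the same reason.
- **Follow-Up Procedure** gives the durations: "The first 5 participants are enrolled for a total of 10 months (an initial 4-month period followed by a 6-month follow-up period"), against 6 months for the other 20. For the first 5, "the baseline for data analysis is defined as the beginning of the 6-month follow-up period at the end of the first preliminary 4-month period". The preliminary phase is described there as serving technical feasibility.
- **Procedure** (text below Figure 2) describes an initial silent month: "The first month is dedicated to algorithm learning: all sensors are functional, but no automatic alert is generated from the platform". It does not say whether the first 5 repeat this month when their analysis period begins.
- **Statistical Analysis** states "The main analysis will be an intent-to-treat analysis" and "The 6-month follow-up period for the 25 participants will allow us to record the number and frequency of alerts generated by the solution". The PPV is to be given overall and for each 2-month period. No separate figure for the first 5 is mentioned.
- **Discussion** (Strengths and Limitations) expects the learning algorithm to perform better over time as user feedback accumulates.
- **Results** reports that the 4-month phase with 5 participants is complete, and describes the second phase by its 20 participants.

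**The concern.** Month 0 means different things in the two groups. For the 20 it is a new installation with an algorithm that has seen no data from that home. For the 5 it follows 4 months of running, during which the solution could be altered. Over the analysed 6 months the 5 contribute months 5 to 10 of operation, and the 20 contribute months 1 to 6.

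Resetting the baseline removes the alerts of the preliminary phase from the count, but leaves the accumulated learning in place. If the sponsor's own expectation of improvement is right, the 5 should show a higher PPV than the 20 over the same nominal period, and pooling would lift the overall figure. A reader who takes the pooled PPV as what a newly equipped household will experience would then be given too favourable a number, and the confidence interval would not reveal it.

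A second, conditional issue follows from the baseline rule. A member of the first 5 who left during the preliminary phase would have no time after the analysis baseline and so could add no alerts.

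**Working it through.** **1. Is the pooling part of the planned precision?**
Inputs from Sample Size: "if a participant triggers 2 alerts on average during the study, with half of them rated as valid". With 25 participants this is 25 × 2 = 50 alerts, of which 25 are valid.
The exact (Clopper-Pearson) 95% interval for x of n runs from the 2.5% quantile of Beta(x, n − x + 1) to the 97.5% quantile of Beta(x + 1, n − x).

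| Method, 25/50 | 95% CI |
|---|---|
| Exact | 35.5% to 64.5% |
| Wald | 36.1% to 63.9% |
| Wald, continuity-corrected | 35.1% to 64.9% |
| Wilson | 36.6% to 63.4% |

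The exact interval reproduces the protocol's 35.5% to 64.5%. The stated precision therefore counts all 25 homes, including the first 5.

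**2. What share do the 5 homes hold?**
- By participants: 5/25 = 20%. With equal alert numbers this is 10 of the 50 alerts.
- By alert-enabled time, if the 5 have already served the silent month and the 20 serve it within their 6 months: 5 × 6 = 30 home-months against 20 × 5 = 100, so 30/130 = 23%.
- If the 5 repeat the silent month, the share returns to 25/125 = 20%.

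The 23% applies to automatic alerts. Both shares assume equal alert rates in the two groups. At half the rate per participant the 5 would supply 2.5/22.5 = 11% of alerts, and at twice the rate 10/30 = 33%.

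**3. How far could the pooled PPV move?**
Pooled PPV = w × PPV(first 5) + (1 − w) × PPV(20). The shift relative to the 20 alone is therefore w × d, where d is the difference in PPV. The documents give no value for d, so a range is assumed.

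| Assumed d | Shift, w = 20% | Shift, w = 23.1% |
|---|---|---|
| 10 points | 2.0 | 2.3 |
| 20 points | 4.0 | 4.6 |
| 30 points | 6.0 | 6.9 |

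With a PPV of 50% in the 20 homes, the pooled value would lie between 52.0% and 56.9%. With d = 0 there is no shift.

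**4. What does separate reporting cost in precision?**
- The 20 alone, 20/40: exact 95% CI 33.8% to 66.2%, half-width 16.2 points against 14.5 for 25/50. The difference is 1.7 points on each side, and the interval is still within the ±20% given under Sample Size.
- The first 5 alone, 5/10: exact 95% CI 18.7% to 81.3%. This is descriptive only.

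**The case against.** The strongest reply has four parts.

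*The objective is not limited to new installations.* The Objectives section asks about the relevance of alerts and how performance evolves. This stands as far as it goes: the pooled PPV is a legitimate summary of the 25 homes as observed. It does not make that figure a fair description of a newly equipped home.

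*The phase is technical, and any fix to the solution also reaches the 20.* This stands. A reader might infer that the system was tuned to those 5 homes. The article speaks only of technical issues and feasibility, and describes no home-specific adjustment of alerts. What remains is the longer operating time, which rests on the sponsor's own expectation of improvement. It bears on the level of the overall PPV as well as on the trend across periods.

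*Staggered enrolment may let changes continue while the 20 join.* Also fair. The 20 are not an untouched validation set, and the claim here is only that none of them starts its analysis period with 4 months already behind it.

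*No loss is reported.* A reader might infer that the 5 are survivors of the preliminary phase, that some left over poor alerts, or that intent-to-treat is broken for a fifth of the sample. The documents support none of these. Results says the phase with 5 participants is complete and mentions no departure. Selection arises only if someone left, and the intent-to-treat label would be affected only for that person.

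It could also be said that subgroup reporting belongs in a statistical analysis plan. But the baseline reset and the pooling are choices the article states, and the point concerns those choices.

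**Conclusion.** The point holds in a limited form. The article does pool 5 homes that have 4 months of prior operation with 20 that have none, and it treats both as starting at month 0. If performance rises with time and feedback, the pooled PPV overstates performance in newly equipped homes.

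The likely size is modest: about 2 to 7 points, which is at most about half the 14.5-point half-width of the protocol's example. This rests on three assumptions: a PPV 10 to 30 points higher in the 5 homes, equal alert rates, and a share of 20% to 23% depending on whether learning restarts. The direction rests on the Discussion's expectation, which the study has yet to show. Selection through the preliminary phase remains a possibility to be closed by a simple count. The change is worth making because it is cheap, not because the pooled figure is shown to be wrong.

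**What to change.** 1. Report the overall PPV with its interval three ways: the 20 newly equipped homes, the first 5, and the pooled 25.
2. Do not rest any statement about newly equipped homes on the pooled figure alone.
3. State how many of the first 5 entered the 6-month period and, if any did not, the reason and how they are counted under the intent-to-treat label.
4. State whether the silent learning month was repeated for the first 5, since this determines their share of alert-enabled time.

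This needs wording and one extra table, with no new visits or participants. The downside is a slightly wider interval for the 20, and a figure for the first 5 that is too imprecise to support a comparison.

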**Figure 1 figure1:**
[figure not shown]
The Standard Protocol Items: Recommendations for Interventional Trials (SPIRIT) flow chart.

### Setting and Participants

All participants must give their written informed consent to take part in the study. Ethical approval was obtained from the Regional Independent Ethics Committee in June 2017 (ID-RCB: 2017-A01002-51).

This solution targets older adults, living with or at risk of functional or cognitive disability and living alone. The detailed inclusion criteria are as follows: aged 75 years or above, living alone at home; frail according to Fried criteria [12] or living with a disability but with an ADL score [13] 3 out of 6 or above; able to walk without help; and provision of written informed consent.

The exclusion criteria are as follows: patient presenting a Mini Mental State Examination (MMSE) <16 out of 30 and without daily care partner support; and under curatorship or guardianship.

Study participants are enrolled through a prescreening procedure on the basis of public administrative records held by several town halls in the region (person aged 75 years or above, living alone at home, and able to walk without help). A clinical research assistant (CRA) then conducts a preinclusion visit by phone. The inclusion visit with the principal investigator (AP) takes place in the Geriatrics Unit at the Toulouse University Hospital.

### Procedure

The solution comprises a set of several minimally invasive sensors installed in the individual’s home (see Table 1 and Figure 2). The solution transmits the data to a remote storage server via a *LIVE Intercom* gateway (a commercially available device). Data are then available for remote consultation by authorized users, that is, patients, care partners, or physicians. The *LIVE Intercom* also allows direct audio communication with the support center (call function) and preliminary data processing before 3G transmission to the remote secure health database. The *minimal sensor set* consists of 4 passive infrared (PIR) sensors to monitor activity (bedroom, kitchen, living room, and entrance hall) and 1 contact sensor on the main entrance door. A sensor on the refrigerator door, a pendant (or bracelet) with a push-button emergency alarm, and a detector under the bed will be available to several participants to assess the technical feasibility. The solution is unobtrusive, and no maintenance is required during the study. Technical support is provided in the event of dysfunction.

**Table 1 table1:** Sensor network description.

Device	Number per house	Technology
Wireless motion detector	4	Passive infrared sensor
Wireless door sensor	1	Magnet proximity sensor
Emergency-alert pendant	1	Push button
Intercom with alert button	1	General packet radio services gateway
Wireless bed rest detector	Optional	4 pressure sensors, 1 under each of the feet of the bed
Wireless physical activity tracker	Optional	Accelerometer

**Figure 2 figure2:**
[figure not shown]
Presentation of the overall solution. In this configuration, the solution comprises 4 passive infrared sensors to monitor activity (bedroom, kitchen, living room, and entrance hall); 1 contact sensor on the main entrance door; 1 cookie sensor on the fridge to monitor door opening; a pendant (or wristband) with a push-button emergency alarm; and a live intercom system (device in the left of the illustration) for direct audio communication with the support center (calling function).

The following data will be monitored: presence (yes/no) in specific rooms, for example, rooms associated with eating, bathing, and sleeping; time spent outdoors; total activity inside the home (estimated by the average number of sensor activations per day) [6]; fridge use; and sleeping patterns.

The solution can trigger 2 different types of alerts. The first consists of *conventional alerts*. They are generated by the participants using an alarm push button or through the intercom system. The second type of alert assessed in this project is automatically triggered by our artificial intelligence algorithm after an initial learning phase (eg, gradual change in sleeping pattern). The sensor-based alerts and the use of the Live intercom calling function are both directed to a telecare worker on a nationwide telecare platform (IMA/Serena) all 7 days a week and 24 hours a day. The telecare worker can suggest a range of actions, from direct contact with the older individual to a phone call to the care partner or to emergency services. The first month is dedicated to algorithm learning: all sensors are functional, but no automatic alert is generated from the platform. Activity data relating to sleeping, eating, and time spent outdoors, and so on, are recorded and analyzed. After the first month, there will be sufficient data to detect unusual behaviors and eventfully trigger an alert. The algorithm used to perform real-time detection of behavioral anomalies is described elsewhere [14].

